**Ethics and dissemination:**

The study has been approved by the Independent Scientific Advisory Committee of the UK Medicines and Healthcare Products Regulatory Agency. Results will be disseminated in scientific publications and at relevant conferences.

Strengths and limitations of this studySelection of electronic health record patients matched to the randomised controlled trial (RCT) patients allows assessment of the ability of non-interventional methods to detect effectiveness of treatments for stroke prevention in atrial fibrillation (AF) within an RCT-analogous population.Combined Clinical Practice Research Datalink (CPRD) Gold and Aurum population broadly representative of the patients prescribed apixaban and warfarin for AF in routine clinical practice in the UK.Some of the criteria that were assessed for ARISTOTLE eligibility may not be well recorded in CPRD.Adherence to medication will need to be assessed based on proxy variables (time covered by prescription for the direct-acting oral anticoagulants, time in therapeutic range based on international normalised ratio measurements for warfarin); the different nature of these proxy variables means the adherence estimates may not be comparable.Ascertainment of outcomes via CPRD is based on recording as part of routine clinical care rather than for specifically detecting study outcomes.

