## Introduction

### Background and rationale

Atrial fibrillation (AF) is a common cause of cardiac arrhythmia with symptoms including palpitations, fainting and shortness of breath; however, some patients may be asymptomatic. The prevalence of AF in the UK is estimated to be around 3%,^1^ increasing from 0.2% in people aged 45–54 years to 8.0% in those 75 and older.^2^ The lack of organised atrial contraction in AF can lead to the formation of thrombi, meaning that patients with AF have a fivefold higher risk of stroke which is an important cause of morbidity and mortality.^3–5^

Current UK guidelines recommend use of prophylactic treatment with anticoagulation medication to reduce the risk of stroke. Warfarin, a vitamin K antagonist (VKA) and the previous standard anticoagulant treatment, has many treatment and dietary interactions requiring frequent monitoring of a patient’s international normalised ratio (INR), to maintain anticoagulant activity within a narrow range (2.0–3.0). Low levels put the patient at a higher risk of stroke while high levels lead to a higher risk of bleeding.^6^ In 2011, the first direct-acting oral anticoagulant (DOAC) dabigatran was approved for the treatment of AF in the European Union (EU); it was anticipated to provide easier to manage long-term anticoagulation therapy for patients with AF given the complex safety profile of warfarin. ARISTOTLE, a pivotal randomised controlled trial (RCT) of the DOAC apixaban, demonstrated superiority over warfarin for both prevention of stroke and safety (major bleeding) among individuals with AF.^7^

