#### ARISTOTLE

ARISTOTLE was a randomised, double-blind trial completed in 2011, comparing apixaban with warfarin in the prevention of stroke and SE. The trial included 18 201 patients with AF and at least one additional risk factor for stroke. The trial was designed to test for non-inferiority of apixaban compared with warfarin, and showed apixaban superiority for (1) the primary outcome of stroke or SE (HR 0.79, 95% CI 0.66 to 0.95),^7^ (2) the safety endpoint of major bleeding (HR 0.69, 95% CI 0.60 to 0.80), and (3) death from any cause (HR 0.89, 95% CI 0.80 to 0.99). The ARISTOTLE findings led to the National Institute for Health and Care Excellence (NICE) guidelines on stroke prophylaxis in patients with AF recommending apixaban as a treatment. Baseline patient characteristics from ARISTOTLE will be used in selection of participants in Objective 1.

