The absolute rates and HR for the outcomes of interest (time to: stroke/SE, MI, major bleeding and mortality) will then be calculated. For the primary outcome (time to stroke/SE) the EHR results will be validated against the ARISTOTLE trial results using the criteria detailed in the Statistical Analysis section (Validation of observational results against ARISTOTLE data).

#### Objective 2

We will select patient groups who would not have been included in ARISTOTLE (and therefore would not have been included in the Objective 1 cohort) or who are under-represented in ARISTOTLE. Specifically, this will include patient groups such as patients with an AF diagnosis in the EHR cohort meeting these additional criteria:

Severe comorbid condition: disease with a likelihood of causing death within 1 year or reasons making participation unpractical (such as dementia).

When matching the apixaban and warfarin patients within the patient groups for this objective, additional baseline variables will be considered compared with the list specified for Objective 1, Step 2; namely the H, A, and B components of the HAS-BLED score (Hypertension, Abnormal renal/liver function, Stroke, Bleeding history or predisposition, Labile INR, Elderly (>65 years), Drugs/alcohol concomitantly) not included for Objective 1 matching due to being ARISTOTLE exclusion criteria. In these special patient populations the same outcomes as Objective 1 will be assessed, with absolute and relative rates calculated separately in each special patient group.

#### Objective 3

We will select all patients with AF who have a prescription for apixaban, warfarin, rivaroxaban or dabigatran in the treatment period (between 1 January 2013 and 31 July 2019). The ARISTOTLE trial criteria will be applied, followed by matching the warfarin, rivaroxaban and dabigatran ARISTOTLE-eligible EHR patients in turn to the trial-eligible EHR apixaban patients following the methodology outlined in Objective 1, Step 3. This process will result in the creation of three trial-eligible EHR cohorts: warfarin users matched to apixaban users, rivaroxaban users matched to apixaban users and dabigatran users matched to apixaban users. Matched cohorts of excluded patient groups will also be constructed to enable pairwise comparisons of treatment effects in these groups using the method outlined in Objective 2. In all cohorts, the same outcomes as Objective 1 will be assessed with both absolute and relative treatment effects compared.

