#### Outcomes

Outcomes to be measured are as follows:

Stroke (ischaemic or haemorrhagic) or SE.Major bleeding.MI.All-cause mortality.Time to AF treatment change.

Outcomes will be ascertained using a combination of CPRD, HES and ONS data.

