#### Missing outcome data

EHR data are shown to be almost complete for mortality.^19^ Patient deaths missing from EHRs are expected to be missing at random equally in both treatment arms, thereby not altering the overall direction of treatment effect. The classification of unspecified stroke type will cause uncertainty in the main safety endpoint and may lead to a lower event rate for major bleeding compared with the trial; this would affect the power but should not affect the treatment effect seen as events are expected to be missing at random from both treatment arms.

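### Equal capture of major bleeds on apixaban and warfarin is assumed but not checked; if bleeds recorded only by the GP count and are recorded more often on warfarin, the bleeding HR shifts in favour of apixaban

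*Protocol article*

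**What the plan says.** The Outcomes section of the protocol article gives one rule for every outcome: "Outcomes will be ascertained using a combination of CPRD, HES and ONS data". It does not say how the three sources are combined or whether a GP code alone is enough for a major bleed. Methods of analysis makes major bleeding the key safety outcome, under on-treatment censoring.

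Three other places bear on capture by arm:

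- Background and rationale describes warfarin as "requiring frequent monitoring of a patient’s international normalised ratio (INR"). Sensitivity analyses plans to compute time in therapeutic range from INR values, so at least part of this monitoring is expected to reach the data.
- The strengths and limitations list says "Ascertainment of outcomes via CPRD is based on recording as part of routine clinical care rather than for specifically detecting study outcomes". The limitation is stated for the study as a whole, not by arm.
- Missing outcome data, discussing strokes of unspecified type, says that a lower bleeding rate "should not affect the treatment effect seen as events are expected to be missing at random from both treatment arms".

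The planned sensitivity analyses cover censoring, switching, adherence, INR control, early adopters, derived index and last-dose dates, and ways of combining Gold and Aurum. None restricts outcomes to HES or ONS, and none compares outcome source between arms. Objective 1, Step 1 limits that cohort to patients with HES and ONS linkage.

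**The concern.** Monitoring for INR is specific to warfarin. Each check is a possible occasion for a bleed to be mentioned and coded, and apixaban patients have no matching occasion. The on-treatment censoring used for bleeding keeps follow-up largely to the period in which warfarin patients are being monitored. Matching on baseline covariates does not address this, because the difference arises after the index date. The benchmark trial was double-blind; this cohort is not.

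What is at stake is the bleeding HR and its comparison with the ARISTOTLE value of 0.69. The compatibility criteria concern stroke/SE only, so a cohort could satisfy them while bleeds were captured unequally. The same outcomes are then used in Objectives 2 and 3. There the apixaban-versus-warfarin comparisons would be exposed, while apixaban versus rivaroxaban or dabigatran would be much less so.

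**Working it through.** **1. Figures in the plan.** The article gives no figure for the capture of bleeds, so there is none to reproduce. Its benchmark for major bleeding is HR 0.69 (95% CI 0.60 to 0.80), from the ARISTOTLE section. The interval is consistent with the estimate: √(0.60 × 0.80) = 0.693. The standard error of the log HR is (ln 0.80 − ln 0.60)/(2 × 1.96) = 0.2877/3.92 = 0.073, used below only as a scale.

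**2. Model.** Let g be the share of true major bleeds that leave no hospital or death record. Let s_A and s_W be the probabilities that the GP records such a bleed on apixaban and on warfarin. Take g as equal in the two arms, and bleeds with a hospital or death record as fully captured in both. If GP-only bleeds count, then approximately

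observed HR / true HR = [(1 − g) + g·s_A] / [(1 − g) + g·s_W].

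**3. Inputs.** The documents give neither g nor s. All values below are assumptions, with s_W = 0.9 throughout.

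| g | s_A = 0.9 | s_A = 0.7 | s_A = 0.5 |
|---|---|---|---|
| 0 | 1.00 | 1.00 | 1.00 |
| 5% | 1.00 | 0.985/0.995 = 0.990 | 0.975/0.995 = 0.980 |
| 10% | 1.00 | 0.970/0.990 = 0.980 | 0.950/0.990 = 0.960 |
| 20% | 1.00 | 0.940/0.980 = 0.959 | 0.900/0.980 = 0.918 |
| 30% | 1.00 | 0.910/0.970 = 0.938 | 0.850/0.970 = 0.876 |

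**4. Second form.** Let c be the number of GP-only events per hospital or death event on apixaban, and r the warfarin-to-apixaban ratio of GP-only recording. The factor is (1 + c)/(1 + c·r). Again with assumed inputs:

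- c = 0.10, r = 1.25: 1.10/1.125 = 0.978
- c = 0.20, r = 1.5: 1.20/1.30 = 0.923
- c = 0.30, r = 1.5: 1.30/1.45 = 0.897

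These lie inside the range of the table.

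**5. Effect on the HR.** From the mildest unequal case to the most extreme (factors 0.990 and 0.876):

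- a true HR of 0.69 would read 0.683 to 0.605;
- a true HR of 0.80 would read 0.792 to 0.701;
- a true HR of 1.00 would read 0.990 to 0.876.

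In the most extreme case, a cohort with a true bleeding HR of 0.80 would appear to reproduce the trial's 0.69.

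**6. Scale.** Against the trial's standard error of 0.073, a factor of 0.959 is a shift of 0.042 on the log scale, about 0.6 standard errors. A factor of 0.876 is 0.132, about 1.8 standard errors. The precision expected in the EHR cohort is not given.

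**7. Validation rule.** It asks that the stroke/SE HR lie between 0.69 and 0.99 and that the upper confidence limit be below 1.52. Bleeding does not enter, so passing the rule says nothing about whether bleeds were captured equally.

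**The case against.** The strongest reply is that the mechanism is inferred. The article does not say that a GP code alone makes a major bleed, and using three sources in combination could mean hospital and death records for bleeding, with CPRD used for items such as treatment change. Code lists and source rules are commonly left to the full protocol. No setting or visit rate is given for INR checks, and an INR value in the record does not show a contact at which bleeds are coded. The expectation of random missingness is written about unspecified stroke type, not contact frequency. Many major bleeds would be expected to reach hospital whatever the monitoring. Even the most extreme case above (0.605) stays inside the trial's interval of 0.60 to 0.80. Absolute event rates will be compared with ARISTOTLE, and routine-care ascertainment is openly listed as a limitation.

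Most of this stands, and it rules out treating the shift as established. It does not supply a check. Comparing absolute rates with the trial could expose an odd bleeding rate, but would not separate unequal recording from a difference in population. The limitation is not discussed by arm, and the statement on missing events gives no reason for equal capture.

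A reader might also infer that Objective 3 would use unlinked patients, because its selection text reads "We will select all patients with AF who have a prescription for apixaban, warfarin, rivaroxaban or dabigatran in the treatment period" without mentioning linkage. The documents do not support that. HES and ONS are listed among the study's data sources, the Outcomes section is not limited to Objective 1, and Objective 3 is to assess the same outcomes by the Objective 1 matching method.

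**Conclusion.** The point holds as an unchecked assumption on the key safety outcome, with a known direction if it fails. Two conditions are needed: GP-only bleeds must count, and they must be recorded more often on warfarin. The observed bleeding HR would then lie below the true HR. The factor is about 0.88 to 1.00 over the assumed inputs, and 1.00 if either condition is absent. The documents do not allow a narrower statement.

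A reader might infer that the bleeding HR is tilted towards apixaban as a matter of fact, or that the missing-data statement is contradicted elsewhere in the article. Neither follows: the article leaves both conditions open, and that statement was written about stroke coding. Nor do the documents show that the validation decision is compromised, since it rests on stroke/SE. The issue is that this decision gives no assurance about bleeding.

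**What to change.** - Add a prespecified analysis of major bleeding, and of stroke/SE and MI, counting only events with a HES admission record or an ONS cause of death.
- Tabulate events found only in CPRD by treatment arm, for each of these outcomes.
- Do the same for the apixaban-versus-warfarin comparisons in Objectives 2 and 3.
- In Missing outcome data, present non-differential capture as an assumption that this analysis checks.

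The Objective 1 cohort is already linked, so the change there needs wording and one outcome flag, with no new data. The restricted analysis will have fewer events, because bleeds managed without admission are lost. For that reason it is proposed alongside the combined definition and not as its replacement. It would not remove any effect of closer contact on referral or admission itself, so agreement between the two definitions would be reassuring but not conclusive.

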#### Covariates

The variables to be considered for matching patients are detailed in the selection of participants for Objective 1 (Step 2).

### Sample size

#### Objective 1

ARISTOTLE included 9120 patients in the apixaban arm, therefore it was estimated a minimum of 15 000 EHR apixaban patients were needed for matching to be feasible. In CPRD Gold, approximately 8400 patients were eligible (January 2018). Aurum (June 2019) contained 23 526 apixaban patients with AF not registered in practices that had previously contributed data to Gold. Assuming the proportion of Aurum patients meeting ARISTOTLE eligibility criteria would be similar to the proportion in Gold (~60%) gave an estimate of 14 115 trial-eligible apixaban patients. Combining Gold and Aurum is therefore estimated to give >22 000 unique trial-eligible EHR apixaban patients.

#### Objectives 2 and 3

From feasibility counts, we are confident we will have sufficient numbers of patients to allow well-powered analyses for Objectives 2 and 3. For example, we estimate the number of people with no evidence of at least one additional risk factor for stroke for Objective 2 would be >3000 people in each exposure group.

### Statistical analysis

#### Methods of analysis

ARISTOTLE used an intent-to-treat (ITT) approach for the primary efficacy analysis and an on-treatment approach for sensitivity analysis and safety outcomes. We will perform equivalent analyses by using two different censoring schemes: a primary censoring scheme censoring 5 years after index date (reflecting the maximum possible follow-up in ARISTOTLE) for the primary effectiveness analyses, and an on-treatment scheme censoring around time of last study drug for the sensitivity analysis and safety outcome. For the on-treatment censoring scheme, date of last exposure will be estimated using patient prescription data—to allow for drug half life, stockpiling of tablets and less than 100% adherence we will add 30 days after the apparent end of treatment.

Demographic and baseline variables will be presented before and after matching steps. As the primary analysis accounts neither for treatment switching nor discontinuation, the proportion of patients discontinuing treatment and time to treatment discontinuation will be tabulated.

The primary effectiveness endpoint is time to first occurrence of confirmed stroke (ischaemic, haemorrhagic or unspecified type) or SE during the study, regardless of whether the subject is receiving treatment at the time (primary censoring scheme). Comparisons will be made according to prescribed treatment (apixaban vs warfarin).

All time to event endpoints will be analysed using a Cox proportional hazards model including treatment group as a covariate and prior warfarin/VKA status (experienced, naïve). Point estimates and two-sided 95% CIs will be constructed for the outcome. Absolute event rates of all outcomes of interest will also be calculated.

Secondary outcomes cover the key safety outcome of major bleeding and the individual outcomes of stroke, SE, MI and mortality. Secondary outcomes other than major bleeding will use the ITT censoring scheme, major bleeding will use the on-treatment censoring scheme.

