**Figure 2 F2:**
[figure not shown]
Flow chart illustrating the assembly of a matched trial-analogous cohort of EHR patients. AF, atrial fibrillation; CPRD, Clinical Practice Research Datalink; EHR, electronic health record.

##### Step 1

We will select all (HES and ONS linked) patients in the EHR cohort (CPRD Gold and Aurum) who would have met the following *inclusion* criteria for the ARISTOTLE study, at least 6 months after patient registration in the database on or prior to the index date:

Diagnosis of AF.Age 18+ years.One or more stroke risk factors (age 75 years or older; prior stroke, transient ischaemic attack or SE; congestive heart failure; diabetes mellitus; hypertension).

In ARISTOTLE, patients randomised to apixaban were new users of apixaban while both treatment arms were allowed to be previous users of warfarin, with patients stratified by prior warfarin/VKA exposure. To mirror ARISTOTLE, we will assess trial criteria for apixaban patients on the date of their first prescription of apixaban while allowing patients prescribed warfarin to become eligible at any warfarin prescription date during the study period; furthermore, we will match ARISTOTLE in the proportion of new versus prevalent users in both treatment arms. We will then exclude patients who meet any of the following ARISTOTLE study *exclusion* criteria prior to their eligible-for-inclusion date:

AF due to reversible causes.Mitral stenosis.Increased bleeding risk.Conditions other than AF requiring chronic anticoagulation.Persistent, uncontrolled hypertension.Active infective endocarditis.Current treatment with aspirin >165 mg/day.Simultaneous current treatment with both aspirin and a thienopyridine.Conditions likely to interfere with participation in the trial or cause death within 1 year.Recent alcohol or drug abuse, or psychosocial reasons making study participation impractical.Recent ischaemic stroke (within 7 days).Severe renal insufficiency.Alanine aminotransferase or aspartate aminotransferase >2× upper limit of normal (ULN) or total bilirubin ≥1.5× ULN.Platelet count ≤100 x10^9^/LHaemoglobin <90 g/L.Pregnancy or breast feeding.

Feasibility counts in Gold found approximately 60% of patients with AF prescribed apixaban met the ARISTOTLE trial criteria. Details of the algorithms used in applying the trial criteria to the EHR data are given in the online supplemental file.

10.1136/bmjopen-2020-042947.supp1Supplementary data

##### Step 2

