We will select a subset of apixaban patients from our EHR pool to create a cohort that matches the ARISTOTLE apixaban participants on a selection of the following baseline characteristics:

Age.Sex.Body mass index (BMI).Systolic blood pressure (SBP).Congestive heart failure or left ventricular systolic dysfunction.Hypertension requiring treatment.Diabetes mellitus.Prior stroke/thromboembolism.Smoking status.Alcohol consumption.Level of renal impairment.Prior VKA/warfarin exposure.Labile INR in prior users of warfarin.Concomitant use of: aspirin, antiplatelet or non-steroidal anti-inflammatory drug, lipid-lowering drug therapy, or CYP3A4 inhibitor.

This step will generate a group of ARISTOTLE-analogous apixaban patients, with similar baseline characteristics to ARISTOTLE subjects at the point of randomisation (n~9000).

The variables selected are expected to influence the likelihood of the outcomes of interest. Exact selection of matching variables will depend on the quality and completeness of the data available and a balance will be struck between matched sample size and balance. Different methods to facilitate selection of a matched cohort will be explored, such as propensity score matching (PSM) and coarsened exact matching (CEM),^13^ a non-parametric method that may give estimates with lower variance and bias for a given sample size compared than other methods.^14^

##### Step 3

The resulting trial matched sample of EHR apixaban patients will be matched to the warfarin ARISTOTLE-eligible EHR patients (figure 2) using a matching method such as PSM or CEM (final method selected based on giving optimal sample size vs balance). Risk set sampling will be employed in order to ensure similar duration of prior VKA/warfarin exposure for the prevalent users in the apixaban and warfarin EHR cohorts. The covariates for consideration in matching between EHR treatment arms or construction of a propensity score (PS) model will include the variables listed in step 2 along with additional EHR variables such as data source (Gold or Aurum), socioeconomic status and comorbidities. Each apixaban patient from the ARISTOTLE-eligible EHR patients will be matched 1:1 with the warfarin EHR patient with the closest match giving a trial-analogous cohort of ~18 000.

##### Step 4

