#### Validation of observational results against ARISTOTLE data

In Objective 1 alone, we will validate the findings from our primary analysis against ARISTOTLE by determining whether results are compatible with the trial results. ARISTOTLE demonstrated superiority of apixaban over warfarin for the primary endpoint (HR 0.79, 95% CI 0.66 to 0.95).^7^ The treatment effect seen with EHR data may be weaker than that seen in ARISTOTLE.

An analysis of EU patients in ARISTOTLE showed a smaller treatment difference for the primary endpoint and death: HR for stroke/SE 0.92 (95% CI 0.56 to 1.52), all-cause death 0.89 (95% CI 0.68 to 1.18). The European Medicines Agency Assessment Report suggested the smaller treatment effect may have been due to superior INR control in the warfarin arm of the EU subgroup (median time in therapeutic range (TTR) 68.93%)^15^; this study could provide additional evidence on this point.

Either a result of superiority or non-inferiority will be considered compatible with ARISTOTLE results. We have set two criteria that must be met to conclude results are consistent with the trial result:

The effect size must be clinically comparable with the ARISTOTLE findings; the HR for time to stroke/SE with the EHR must be between 0.69 and 0.99. This range is not symmetrical around the ARISTOTLE estimate of 0.79 as it is anticipated the treatment effect in routine clinical care may be weaker than that seen in the optimised setting of a clinical trial.The upper limit of the 95% CI for the rate ratio must be less than 1.52 (upper limit in the EU subgroup of ARISTOTLE).

In addition, if the upper limit of the 95% CI is less than 1 then superiority of apixaban versus warfarin will be concluded.

In order to understand the extent to which the EHR population resembles the ARISTOTLE trial population the absolute event rates of the outcomes will be compared.

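### The Cox model adjusts only for prior VKA use and names no variance for the matched design, so comparator reuse could affect the superiority conclusion and residual imbalance the validating HR

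*Protocol article*

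**What the plan says.** Under Methods of analysis: "All time to event endpoints will be analysed using a Cox proportional hazards model including treatment group as a covariate and prior warfarin/VKA status". Of the intervals it says: "Point estimates and two-sided 95% CIs will be constructed for the outcome". It names no variance estimator and no further covariates.

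The cohort is built under Selection of participants, Objective 1. Step 1 differs by arm. Apixaban patients enter at their first apixaban prescription and may be earlier warfarin users. For the comparators the protocol speaks of "allowing patients prescribed warfarin to become eligible at any warfarin prescription date during the study period". Step 3 then says: "Each apixaban patient from the ARISTOTLE-eligible EHR patients will be matched 1:1 with the warfarin EHR patient with the closest match". The size expected from this is put as "giving a trial-analogous cohort of ~18 000". It adds: "Risk set sampling will be employed in order to ensure similar duration of prior VKA/warfarin exposure for the prevalent users". The Step 3 covariates "will include the variables listed in step 2 along with additional EHR variables such as data source (Gold or Aurum), socioeconomic status and comorbidities". Whether matching is with or without replacement is not stated. The matching method is left open and is to be chosen by weighing sample size against balance.

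Plan for addressing confounding relies on matching for measured confounders. Baseline tables before and after matching are promised, but no balance threshold is given and no step follows if imbalance remains.

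Under Validation of observational results against ARISTOTLE data, validation needs an HR for stroke/SE between 0.69 and 0.99 and an upper 95% limit below 1.52. In addition, "if the upper limit of the 95% CI is less than 1 then superiority of apixaban versus warfarin will be concluded".

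**The concern.** The model has the form that suits a trial stratified by prior VKA exposure, as Step 1 says ARISTOTLE was. Here the patients are matched, not randomised, and their records may not be independent. Two things follow.

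1. **Precision.** Pairs matched on prognostic variables have correlated outcomes, which makes the model-based variance slightly too large. A warfarin patient used in several pairs contributes the same events more than once, which makes it too small. A person who is first a warfarin comparator and later an apixaban patient links the two arms. Because the primary scheme ignores switching, a later stroke could count in both. The superiority statement rests on the CI.
2. **Bias.** Measured imbalance left after closest matching goes straight into the HR, because the model contains none of the matching covariates except prior VKA status. The HR point estimate decides validation, and validation opens the way to Objectives 2 and 3.

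**Working it through.** **Inputs from the protocol.** About 9000 apixaban patients matched 1:1, so 2 × 9000 = 18 000, as stated. ARISTOTLE HR 0.79 (0.66 to 0.95). Validation limits 0.69, 0.99 and 1.52; superiority limit 1. The protocol gives no event count or power for the EHR cohort, no size for the warfarin pool and no extent of reuse. Event rates, prognostic spread and reuse below are therefore assumptions.

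**Step 1: a reference precision.** SE(log HR) = ln(0.95/0.66)/(2 × 1.96) = 0.0929. The CI midpoint is √(0.66 × 0.95) = 0.792, which agrees with the stated 0.79. By 4/SE² this corresponds to about 463 events. The SE is used below only as an illustration.

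**Step 2: pairs without reuse.** Simulation of 9000 pairs, 400 runs each, HR 0.79, assumed rate 1.6% per year, treatment as the only model term. For a log-hazard SD shared within pairs of 0.5, 0.8 and 1.2, the ratio of cluster-robust to model-based variance was 0.99, 0.97 and 0.92. Coverage of the model-based CI, measured around the mean simulated estimate, was about 95.5–96%. The CI is slightly too wide.

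**Step 3: comparators reused.**

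| Assumed reuse | True/model-based variance | Model-based coverage |
|---|---|---|
| 30% of comparator slots filled by people used twice (4500 pairs, HR 0.85) | (0.127/0.117)² = 1.18 | 93.5% |
| 60% of slots, same setting | (0.128/0.117)² to (0.131/0.117)² = 1.20 to 1.25 | 92.8% |
| 9000 draws with replacement from 9000/1.2 = 7500 people (HR 0.79, SD 0.8) | 1.48 | 87.5% |
| 9000 draws with replacement from 9000/2 = 4500 people, same setting | 1.82 | 83.5% |

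The last two rows are heavy reuse: about 7500 × (1 − e^−1.2) = 5241 and 4500 × (1 − e^−2) = 3891 distinct comparators fill 9000 slots.

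A hand check on those two rows: reuse multiplies the warfarin part of the variance by Σk²/Σk, where k is the number of times a person is used. This is 1 + 1.2 = 2.2 and 1 + 2 = 3.0. With HR 0.79 the warfarin part is 0.79/1.79 = 0.44 of the total. The ratios are then 0.56 + 0.44 × 2.2 = 1.53 and 0.56 + 0.44 × 3.0 = 1.88. The simulated values lie a little lower, which is the direction expected from pairing.

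**Step 4: effect on superiority.** For a variance ratio r, the upper limit at HR 0.79 is 0.79 × exp(1.96 × 0.0929 × √r), and superiority needs an HR below exp(−1.96 × 0.0929 × √r).

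| r | Upper limit at HR 0.79 | HR needed for superiority |
|---|---|---|
| 0.92 | 0.941 | 0.840 |
| 1.00 | 0.948 | 0.834 |
| 1.18 | 0.963 | 0.821 |
| 1.48 | 0.986 | 0.801 |
| 1.82 | 1.010 | 0.782 |

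**Step 5: effect on the 1.52 limit.** At the largest admissible HR the upper limit is 0.99 × exp(1.96 × 0.0929) = 1.19; with r = 1.82 it is 1.27. To reach 1.52 the SE would have to be ln(1.52/0.99)/1.96 = 0.219. That is 2.35 times the reference SE, 5.5 times the variance, or about 84 events. Errors of the size in Step 3 do not come near it.

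**Step 6: residual imbalance and the HR.** A standardised difference of 0.1 on a prognostic score with an assumed log HR of 0.3 to 0.7 per SD multiplies the HR by exp(−0.03) = 0.970 to exp(−0.07) = 0.932, or by the inverse if the imbalance runs the other way. A 2–5 point difference in a binary factor (assumed prevalence 19%, HR 2–2.5) shifts it by about 2–6%. Against the validation range:

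- An HR of 0.95 raised by 5% becomes 0.9975 and fails.
- At the upper edge, HRs above 0.99 × 0.970 = 0.961 (3% shift) or 0.99 × 0.932 = 0.923 (7% shift) could be pushed out.
- At the lower edge, HRs below 0.69/0.970 = 0.711 or 0.69/0.932 = 0.740 could be pushed out.
- ARISTOTLE's own 0.79 would stay inside (0.737 to 0.847 at 7%). The EU subgroup's 0.92 would stay just inside (0.92/0.932 = 0.987).

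**The case against.** The best defence is that a journal article commonly leaves the variance estimator to the full protocol or SAP. A reader might infer that patients are to be analysed as independent. The document does not say so; this would be a reading of silence.

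A reader might also infer that the CIs are simply wrong. That is not supported. The natural reading of about 9000 becoming about 18 000 is roughly 9000 distinct comparators, and then the CI errs slightly on the safe side. The Step 1 wording says when a warfarin patient may qualify, not that one person enters repeatedly. Risk set sampling is there to align prior VKA duration. Reuse is left open, not planned. A person in both arms adds positive covariance between the arms, which by itself makes the model-based CI too wide.

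Nor do the documents show that poor matches will be kept. Coarsened exact matching prunes, a caliper is compatible with closest matching, the cohort size is approximate, and balance will be tabulated. Treatment plus prior VKA status is a coherent model if balance is good, and it mirrors ARISTOTLE. Adding covariates makes the HR conditional and so a little less comparable with 0.79.

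All of this limits the claim. What remains is that the adjustment set is stated here, matching is the only named control of measured confounding, size is traded against balance with no threshold, and none of the listed sensitivity analyses covers imbalance left after matching or repeated use of a person.

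**Conclusion.** The point holds as a should-fix improvement. The CI can be materially too narrow only if people are reused. In the assumed scenarios the true variance is 1.18 to 1.82 times the model-based one, and at HR 0.79 and SE 0.0929 only the heaviest reuse reverses superiority. Without reuse the error is small and conservative.

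A reader might take the CI to decide validation as well. The figures do not support that, because 1.52 is far from binding. Validation depends on the point estimate, where an assumed residual imbalance of 0.1 SD on a prognostic score moves the HR by about 3–7%. This matters for estimates near 0.69 or 0.99, and it is a risk, not a certainty.

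The sizes rest on assumed event rates, prognostic spread, reuse and imbalance. The effect on the HR of one event counting in both arms was not quantified.

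**What to change.** - Keep the Cox model with treatment and prior VKA status, but compute the CIs with robust (sandwich) variance clustered on matched set and on person, so that someone who appears twice or in both arms is not counted as separate people.
- State whether a warfarin patient may be reused and whether a person may appear in both arms. Report how many do.
- Add to the Cox model any Step 3 covariate with a post-matching standardised difference above 0.1, at least as a prespecified sensitivity analysis, and read that HR against 0.69–0.99.

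A caliper is optional. It would cost some apixaban patients, and that is the size-versus-balance choice Step 3 already leaves open.

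The cost is a few lines of text and code on data already held. The adjusted HR is conditional on covariates, which differs little from the marginal HR if events are rare; keeping it as a sensitivity analysis leaves the main estimate comparable with ARISTOTLE.
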